**Figure 1 f1:**
[figure not shown]
Trial design flow chart. The study population includes high-risk ALL or AML pediatric patients candidate to haplo-HCT and with an expected risk of leukemia relapse after transplantation ≥ 50%. The donor, once screened and deemed eligible, will undergo leukapheresis to obtain PBMC cryopreserved in multiple vials. Depending on the availability of cryopreserved LB patients will be assigned to the treatment with anti-leukemia CTLs (experimental arm), otherwise they will proceed to standard treatment with DLI (control arm).

### Study objectives

The primary objective will be safety, measured as the incidence of acute GVHD after treatment. Acute GVHD will be diagnosed and graded according to the NIH criteria. Grade II-IV acute GVHD will be expressed as cumulative incidence considering disease relapse and death in remission without GVHD as competing events. The key secondary objective will be preliminary efficacy, measured as the incidence of relapse, (REL) defined as the time from HCT to the date of disease relapse, will be calculated at 3, 6, 9, 12–18 and 24 months after HCT and expressed as cumulative incidence considering death in remission as competing event.

### Patients’ selection

Fifteen pediatric subjects will be enrolled in this study after obtaining informed consent. The study population will comprise any infant (1 month- 24 months), child (2–11 years) and teenager (12–18 years) affected by high-risk ALL or AML, candidate to an haplo-HCT and with an expected risk of leukemia relapse after transplantation ≥ 50% according to the available literature data. In **Tables 1**, **2** patients’ inclusion and exclusion criteria are reported, respectively. Eligible donors are HLA haploidentical relatives, including but not limited to biological parents, siblings, or half-siblings. Matching will be determined by class I and class II DNA typing. In **Table 3**, donor inclusion and exclusion criteria are reported.

**Table 1 T1:** Inclusion criteria for ALL and AML patients’ enrolment.

ALL patients’ inclusion criteria	AML patients’ inclusion criteria
Age ≥ 1 month and ≤ 18 years	Age ≥ 1 month and≤ 18 years
Life expectancy > 12 weeks	Life expectancy > 12 weeks
ALL in first morphological remission but with a positive MRD≥ 1 x 10–^3^ before HCT	AML in first morphological remission and with a flow cytometry MRD at the end of induction therapy ≥ 0.1%;
ALL in second morphological remission after a high-risk relapse (patients belonging to the S3-S4 BFM risk group), independently of the level of MRD	AML in first morphological remission and with high-risk disease according to the presence of unfavorable cytogenetic or molecular aberrations
ALL in second morphological remission with any MRD positivity before HCT	AML in first morphological remission after a primary induction failure
ALL in third or subsequent morphological remission, independently of the level of MRD	AML in second morphological remission
ALL patients not in morphological remission at time of HSCT	AML in third or subsequent morphological remission
Pre-HSCT Lansky/Karnofsky score ≥ 40%.	Pre-HSCT Lansky/Karnofsky score ≥ 40%.
HIV negativity	HIV negativity

**Table 2 T2:** Exclusion criteria for patients’ enrolment.

Patients’ exclusion criteria
Ongoing active acute GVHD or chronic GVHD due to a previous allograft
Presence of clinically active infectious disease (including positive HIV serology or viral RNA)
Severe cardiovascular disease (arrhythmias requiring chronic treatment, congestive heart failure or left ventricular ejection fraction <40%)
Liver dysfunction (AST/ALT ≥ 3 times institutional upper limit normal value –ULN- or bilirubin > 3 times ULN)
Renal dysfunction: serum creatinine > 1.5 times ULN or calculated creatinine clearance < 60 ml/min/1.73 m^2^
End stage irreversible multi-system organ failure.
Other active malignancy.
Pregnant or breast feeding female patient
Lack of parents’/guardian’s written informed consent for children who are minors or lack of written informed consent for patients aged 18 y

**Table 3 T3:** Parameters for batch release.

Parameter	Methodology	Cutoff value
Sterility	Automated culture method	negative
Bacterial endotoxin content	LAL test	<0.5 EU/ml
Mycoplasma content	RT-PCR	absent
Viability	Trypan blue staining	>80%
Genotype identity	Molecular analysis	- molecular identity between ATMP, starting material and donor - absence of foreign genetic material
Phenotype	Flow cytometry analysis	T-CD3+ ≥ 75%, CD3-neg/CD56 + 0-25%, CD19+/CD20+ CD14+ ≤ 5%
Potency	Cytotoxicity by ^51^Cr assay ^¶^	% specific lysis >45%

Microbiologic controls of ATMP were performed under aseptic conditions, according to European Pharmacopoeia (Eu.Ph.) guidelines. ¶ Potency was evaluated by CD3-redirected assay against P815 cell line.

### Anti-leukemia CTLs production

The production of anti-leukemia CTLs is carried out in compliance with current European GMP regulations. The active substance consists of donor T lymphocytes with cytotoxic capacity directed against LB of the patient for whom the cell therapy medicinal product is intended. Starting material consists of mononuclear cells obtained by HCT donor. The donor once screened and deemed eligible, before mobilization for hematopoietic stem cell collection, will undergo leukapheresis, following the established regulatory guidelines for monitoring and institutional standard procedures for collection. PBMC will be isolated by density gradient centrifugation and cryopreserved. Patients’ LB are collected and cryopreserved at the time of leukemia diagnosis/recurrence. The methodological approach for the production of anti-leukemia CTL was optimized over time and consists in three different phases: priming, leukemia-specific stimulation and rapid antigen independent expansion. Priming is based on the use of donor DC, derived from CD14+ cells cultured four days in the presence of rGM-CSF and IFN-α2b, pulsed with irradiated (200Gy) apoptotic patients’ LB as the source of leukemia associated antigens, as previously described (31) in medium supplemented with appropriate concentration of IL-7, IL-12, IL-15 and IFNα 2b (34).

As shown in **Figure 2**, after priming and leukemia-specific stimulation, CTLs undergo the 1^st^ round of antigen independent expansion. After leukemia-specific stimulation, CTLs are recovered and can be cryopreserved or undergo the first round of rapid expansion. Anti-leukemia CTLs recovered after the 1^st^ round of rapid expansion are cryopreserved in vials. Batch 1 of the ATMP can be administered to patients or, if necessary, undergo a subsequent round of rapid expansion for the production of further batches of ATMP. Following this protocol, virtually billions of CTLs can be obtained for each patient. The time necessary to expand CTL batch 1 is just over a month, while subsequent batches are produced in about two weeks. At the end of the culture, CTLs mostly contain CD3+/CD8+ T lymphocytes, and a low percentage of CD3+/CD4+ T lymphocytes. ATMP batches are subjected to microbiological and biological quality controls (QC) before product release. Microbiological QC include testing for sterility, endotoxin by LAL assay and Mycoplasma by RT-PCR. Biological QC include: i) count of viable cells before and after cryopreservation; ii) immune phenotype characterization; iii) genotypic identity; iv) potency by means of CD3-redirected cytotoxicity test (**Table 3**). After confirming the stability of ATMP up to eight years after cryopreservation, biological CQ that included evaluation of phenotype and potency are performed on cryopreserved ATMPs as they represent the product that will be infused.

**Figure 2 f2:**
[figure not shown]
Protocol of production of anti-leukemia CTL. **(A)** After priming and leukemia-specific stimulation, CTL underwent the 1**
^st^
** round of antigen independent expansion. Anti-leukemia CTL recovered after the 1^st^ round of rapid expansion were cryopreserved in several vials. Some vials represent the batch 1 of ATMP and can be infused to patients or alternately undergo a 2**
^nd^
** round of rapid expansion **(B)**, to produce the next batches of ATMP. Batch 1 and subsequent ones were subjected to microbiological and biological quality controls for the release of ATMP.

### Study procedures

Anti-leukemia CTLs will be administered at progressively increasing doses every 3 weeks according to the following schedule: 5x10^4^/kg; 1x10^5^/kg; 5x10^5^/kg; 1x10^6^/kg; 2x10^6^/kg; 4x10^6^/kg; 8x10^6^/kg and 8x10^6^/kg. Treatment will start within 60 days after transplantation, and it will continue for the next 6–8 months, depending on the frequency of CTL infusions. In the absence of complications, the minimum number of infusions is eight. Considering the high risk of recurrence, based on the clinician’s judgement, it will be possible to administer subsequent monthly CTL infusions, at the same dose used for the last administration, until month +12 from HCT.

Anti-viral prophylaxis will be administered per standard site procedures. During the treatment, the administration of corticosteroids should be avoided, unless necessary, and in this case it will be recorded.

In case of development of grade I acute GVHD, subsequent CTL administrations will be delayed by 1 week and CTLs will be given at the immediately lower dose than that which preceded the occurrence of GVHD. Subsequently, the treatment will continue with the same schedule. In case of development of acute GVHD of grade ≥ II, treatment will be stopped until complete resolution of GVHD. Subsequently, based on the clinician’s judgement, anti-leukemia CTLs may be resumed, starting from the immediately lower dose than that which preceded the occurrence of GVHD, every 3 weeks with the same schedule. Subjects who develop grade I or II skin GVHD (up to Stage 3 skin GVHD without any gut or liver involvement) will be treated with topical steroids and/or other standard of care (SOC) therapies. Subjects who experience Grade III skin and/or Grade II- III non-cutaneous GVHD will be treated with standard therapy. Chronic GVHD will be treated according to SOC. In **Table 4** the stopping rules are reported.

**Table 4 T4:** Stopping rules.

Stopping rules
Development of grade III-IV acute GVHD in 2 out of the first 4 patients treated.
Development of any severe adverse event (AE) in 2 out of the first 4 patients treated.
Development of any serious adverse event (SAE) in 2 of the 4 patients of each subsequent group of 4 patients.
Incidence of grade II-IV acute GVHD ≥ 40% in the enrolled patient population.
Incidence of chronic GVHD (mild, moderate or severe) ≥ 40 in the enrolled patient population.

A screening evaluation that includes clinical and laboratory assessment will be performed at enrollment, prior to each CTL infusion, and at day 30, 90, 180, 360, 540 and 720 from HCT (if they do not coincide with CTL infusions). Prior to each CTL infusion, chimerism analysis and immunological follow up on peripheral blood will be performed. The immunological follow up will include evaluation of the percentages of circulating T, Treg, B and NK subsets, interferon-gamma secreting cells in response to LB stimulation *in vitro* on peripheral blood. MRD evaluation on bone marrow will be performed at baseline, at +90, +180 and +360 days after Haplo-HCT.

### Toxicity evaluation

Safety assessments will consist of monitoring protocol-defined endpoints, such as acute GVHD, measurement of protocol-specified hematology, clinical chemistry variables, vital signs and other protocol-specified tests that are deemed critical to the safety evaluation of the ATMP. All adverse events (AEs) and serious adverse events (SAEs) will be recorded. AEs will be collected for 30 days following the final infusion of anti-leukemia CTLs. All SAEs will be collected until 90 days following the last anti-leukemia CTL infusion. After this period, investigators will report SAEs considered related to the study treatment.

### Sample size and data analysis

The sample size is calculated based on the primary safety endpoint, using the single stage method for phase II studies proposed by Fleming (35). This method has been primarily designed to provide sufficient clinical experience to support the design of later-stage clinical development such as phase III studies. We assumed a maximum proportion P0 of patients developing GVHD, for patients receiving the standard treatment (DLI), of 40% based on our previous experience, and on data reported in the literature (H0). We consider 10% as the maximum proportion P1 of patients developing GVHD for the study treatment (CTLs) to consider the study treatment for preliminary success (H1). A sample size of 15 patients (including a dropout of 1 patient) will be able to reject H0 with a power of 80% and a type I error of 5%. If the number of responses at the end of the study is ≤ 2, H0 will be rejected; if the number of responses is > 2, H1 will be rejected. Quantitative variables will be reported as the median value and range, while categorical variables will be expressed as absolute numbers and percentage. The demographic and clinical characteristics of patients and controls will be compared using the Chi-square test or Fisher’s exact test for categorical variables, while the Mann-Whitney rank sum test or the Student’s t-test will be used for continuous variables as appropriate. Overall survival (OS) and event-free survival (EFS) will be calculated according to the Kaplan-Meier method, while the risk of acute and chronic GVHD, relapse and death in remission, defined as non-relapse mortality (NRM) will be calculated as cumulative incidences (CI) in order to adjust the analysis for competing risks. Comparisons between different OS and EFS probabilities will be performed using the Log-Rank test, while the Gray’s test will be used to assess, in univariable analyses, differences between cumulative incidences. All results will be expressed as probabilities (%) or cumulative incidences (%) and 95% confidence interval (95% CI), at 3, 6, 9, 12, 18 and 24 months from HCT. P values < 0.05 will be considered statistically significant. Statistical analysis will be performed using NCSS [NCSS 10 Statistical Software (2015). NCSS, LLC. Kaysville, Utah, ncss.com/software/ncss.] and MP/15 (StataCorp LP, [name] (http://www.stata.com).

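### The cut-off of two GVHD events has no denominator and holds the 5% type I error only with 14 or 15 evaluable patients

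*Protocol article*

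**What the plan says.** The section on sample size and data analysis uses a Fleming single-stage design for the primary safety endpoint. The null rate is given by "We assumed a maximum proportion P0 of patients developing GVHD, for patients receiving the standard treatment (DLI), of 40" per cent, and the target by "We consider 10% as the maximum proportion P1 of patients developing GVHD for the study treatment (CTLs", set at 10%. The article says "A sample size of 15 patients (including a dropout of 1 patient" and that this number "will be able to reject H0 with a power of 80% and a type I error of 5" per cent. The decision follows: "If the number of responses at the end of the study is ≤ 2, H0 will be rejected", and with more than 2 the alternative is rejected. The word responses can only mean GVHD events here.

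Three other statements bear on who is counted:

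- Patients' selection: "Fifteen pediatric subjects will be enrolled in this study after obtaining informed consent". They are enrolled as candidates for haplo-HCT, that is, before transplantation.
- Study procedures: CTLs start within 60 days after transplantation and continue for 6–8 months, and "Anti-leukemia CTLs will be administered at progressively increasing doses every 3 weeks according to the following schedule".
- Study objectives: "Grade II-IV acute GVHD will be expressed as cumulative incidence considering disease relapse and death in remission without GVHD as competing events".

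Trial design puts the expected relapse risk after haplo-HCT at 50% or more. The article gives no denominator for the count, no cut-off for any other evaluable number, and no replacement rule.

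**The concern.** A fixed count of adverse events becomes easier to satisfy as fewer patients are available to have one. Here a low count is the favourable result, so each patient lost beyond the planned one raises the chance of declaring success when the true GVHD rate is 40%. Power at 10% also rises as patients are lost (0.842 at 14, 0.866 at 13), so nothing in the stated operating characteristics warns of the problem.

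A related question is how a patient who relapses early enters the count. If that patient stays in as a non-event after little exposure, the count is diluted in the same direction. At stake is the primary safety decision in children, taken on at most 15 patients.

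**Working it through.** **Inputs.** P0 = 0.40, P1 = 0.10, 15 patients with 1 dropout, cut-off c = 2, type I error 5% and power 80% (sample size section). The rule points one way, so the error is one-sided.

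**Formula.** With n evaluable patients and event rate p, P(X ≤ c) = Σ from k = 0 to c of C(n,k) p^k (1−p)^(n−k). Type I error is this sum at p = 0.40; power is the sum at p = 0.10.

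**Step 1: the plan's own figure.** At n = 14 and p = 0.40: 0.6^14 + 14 × 0.4 × 0.6^13 + 91 × 0.16 × 0.6^12 = 0.0008 + 0.0073 + 0.0317 = 0.0398. Power is 0.842. At n = 15 the values are 0.0271 and 0.816. The smallest exact design with error ≤ 5% and power ≥ 80% is n = 14 with c = 2, so the plan reproduces.

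**Step 2: the same cut-off at other evaluable numbers.**

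| Evaluable n | Type I error, ≤ 2 | Power, ≤ 2 | Type I error, ≤ 1 | Power, ≤ 1 |
|---|---|---|---|---|
| 15 | 0.027 | 0.816 | 0.005 | 0.549 |
| 14 | 0.040 | 0.842 | 0.008 | 0.585 |
| 13 | 0.058 | 0.866 | 0.013 | 0.621 |
| 12 | 0.083 | 0.889 | 0.020 | 0.659 |
| 11 | 0.119 | 0.910 | 0.030 | 0.697 |
| 10 | 0.167 | 0.930 | 0.046 | 0.736 |

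The 5% limit is passed at the second lost patient.

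**Step 3: how plausible is a second loss?** The article gives no rate of patients enrolled but never infused, so this is an assumed range. With a chance d per patient, P(at least 2 of 15 lost) = 1 − (1−d)^15 − 15d(1−d)^14. This is 17% at d = 5%, 45% at 10% and 83% at 20%.

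**Step 4: early relapses kept as non-events.** This is an alternative to Step 2 for any given patient, who either leaves the denominator or stays in it. Assume that a share q of the 15 relapse before GVHD could occur, and that 40% applies to the rest. The effective rate is 0.40 × (1−q), and the type I error is:

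- q = 5%: rate 0.38, error 0.038
- q = 10%: rate 0.36, error 0.053
- q = 20%: rate 0.32, error 0.096
- q = 30%: rate 0.28, error 0.165

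The dosing schedule shows why early relapse could matter. In units of 10^6/kg the first three of eight infusions sum to 0.05 + 0.1 + 0.5 = 0.65 of a total of 23.65, or 2.7%. The article does not say how GVHD risk relates to cumulative cell number, so this is context and not an input.

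**Step 5: the other reading of the 40%.** If the 40% for DLI is a crude proportion from patients with a similar relapse pattern, relapsed patients are already event-free in it. Counting them the same way here matches the null, and the error stays at 0.027 (n = 15) or 0.040 (n = 14).

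**The case against.** The strongest reply is that the design is right as stated. The cut-off directly follows the sentence on 15 patients with one dropout and reads naturally as the rule for that number. The planned loss is covered, and at 13 patients the excess is small (0.058). This stands: a reader might infer that the design fails to hold 5%, and the article does not support that.

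A reader might also infer that the plan counts early relapses as GVHD-free, or that half the patients will be lost early. Neither is stated. The competing-event wording concerns the cumulative incidence estimate, and the count rule does not refer to it. The article does not say that relapse ends infusions. The 50% relapse risk has no time horizon. Step 5 shows that the dilution disappears if the 40% is already net of relapse, and the controls are described as having the same prognosis. So Step 4 is conditional.

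Failure of batch release is not shown to be a likely cause of loss: the pre-clinical section reports that 51 batches met the biological cut-offs.

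Evaluability and replacement rules may sit in the full protocol. If so, the decision rule needs only to cite them. But the article does state the threshold, and as stated it is valid at only two evaluable numbers.

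Stopping rules and cumulative incidences with confidence intervals give further protection. They do not repair this threshold: 2 events among 10 patients is 20%, well below the 40% GVHD stopping limit at the final count.

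**Conclusion.** The point holds in a limited form. The ≤ 2 rule keeps the stated 5% with 14 or 15 evaluable patients and exceeds it from the second non-evaluable patient, reaching 0.083 at 12 and 0.167 at 10. This rests only on the plan's own P0 and exact binomial arithmetic. That losses will exceed one is plausible from the timing of enrolment and the relapse risk, but the article gives no rate.

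The inflation through early relapse (0.053 to 0.165 for 10% to 30% early loss) needs two further assumptions: that these patients stay in the count as non-events, and that the 40% is not already net of relapse. The article settles neither.

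**What to change.** 1. Define the denominator of the primary count without reference to outcome, for example all patients given at least one CTL infusion.
2. State the cut-off by that number: ≤ 2 events for 14–15 patients, ≤ 1 for 10–13 (type I error 0.013–0.046, power 0.62–0.74). Below 10, ≤ 1 no longer holds 5% (0.0705 at 9), so the plan should say what is then concluded.
3. State whether P0 = 40% is a crude proportion net of relapse, and how early relapse or death enters the count.
4. Report, as a sensitivity analysis only, the GVHD proportion among patients who did not relapse or die early, with early defined in advance.

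Replacing never-infused patients until 14 have been infused is an alternative to item 2. It keeps 0.040 and 0.842 at the price of longer accrual.

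The primary set should not keep every GVHD case while dropping event-free patients who miss a minimum number of infusions. Its denominator would depend on outcome: a true 10% among all treated becomes 0.10/0.70 = 14% if 30% are dropped in this way, and P0 and P1 would no longer apply to it.

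The cost is one definition and a short table. The downside is that stated power falls below 80% if fewer than 14 are evaluable.

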## Methods and analysis

### Trial design

Leuk-001 is a Phase I/II, monocentric, open label, non-randomized, prospective clinical trial of donor-derived anti-leukemia CTLs in pediatric haplo-HCT recipients transplanted for ALL or AML and with a risk of leukemia relapse after haplo-HCT ≥ 50%. The outcome of treated patients will be compared with that of pediatric recipients of haplo-HCT with the same disease characteristics and prognosis, who received infusions of unmanipulated DLI. Patients will be assigned to the treatment with anti-leukemia CTLs (experimental arm) or to standard treatment with DLI (control arm) based on the availability of cryopreserved viable LB collected at the diagnosis or at relapse, necessary for the production of anti-leukemia CTLs (**Figure 1**). Therefore, this will be the only difference between the study population and the control population.

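### Results are timed from HCT while the comparison is worded by infusion received, and the start of the acute GVHD risk period is stated in two ways

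*Protocol article*

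**What the plan says.** **Who is compared.** Under Trial design, patients are allocated "based on the availability of cryopreserved viable LB collected at the diagnosis or at relapse", which can be known before transplant. The same section then says that "The outcome of treated patients will be compared with that of pediatric recipients of haplo-HCT" with the same disease features who were given unmanipulated DLI. The Discussion again describes the controls as a cohort treated with DLI.

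**When the clock starts.** Study objectives gives relapse as "defined as the time from HCT to the date of disease relapse". Sample size and data analysis lists OS and EFS (Kaplan-Meier, Log-Rank) and acute GVHD, chronic GVHD, relapse and NRM (cumulative incidence, Gray's test), and reports all of them "at 3, 6, 9, 12, 18 and 24 months from HCT". It describes no landmark, delayed entry or time-dependent treatment.

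**When treatment starts.** Study procedures: "Treatment will start within 60 days after transplantation". No minimum delay is given, and no timing is given for DLI.

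**The primary endpoint.** Study objectives describes safety as "measured as the incidence of acute GVHD after treatment". The analysis section puts acute GVHD on the HCT clock. Its decision rule (reject H0 if two or fewer patients have GVHD) does not say from when cases count.

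**The concern.** Two separate problems follow from the HCT clock.

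1. *Guaranteed time.* If a patient enters the analysis because an infusion was given, the interval from HCT to that infusion is free of death by construction. It is also free of relapse if patients who relapse first are not infused. Starting the curve at HCT credits that interval to the group. Absolute survival and relapse estimates become too favourable, and the comparison is distorted if the two arms are infused at different times.

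2. *Attribution of GVHD.* The listed GVHD exclusion (Table 2) covers only disease from a previous allograft, so GVHD from the study graft can occur before the first CTL. Whether such a case counts depends on which section is followed. With a limit of two cases among about 14 patients, a single one uses half of the allowance.

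The two effects run in opposite directions. The first flatters survival and relapse; the second penalises the product on safety.

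**Working it through.** **Step 1. Reproduce the plan's own figure.** Inputs from Sample size and data analysis: P0 = 40%, P1 = 10%, 15 patients including 1 dropout (14 evaluable), reject H0 at two or fewer cases. With X binomial (14, p):

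- Type I error = P(X ≤ 2 | p = 0.40) = 0.0398.
- Power = P(X ≤ 2 | p = 0.10) = 0.8416.
- n = 13 fails, with a type I error of 0.0579.

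So 14 + 1 reproduces exactly, and the sample size is not in question.

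**Step 2. Guaranteed time (illustration).** The ≥ 50% relapse risk under Trial design has no time horizon, so a horizon must be assumed. Assumptions: constant hazard, 50% relapse by 24 months, no competing deaths, nobody infused after relapse, everyone infused on the same day d.

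- λ = ln 2 / 24 = 0.0289 per month. Day 60 is m = 60 / 30.4375 = 1.97 months.
- All patients from HCT: F(t) = 1 − exp(−λt).
- Infused patients only, still timed from HCT: 1 − exp(−λ(t − m)).

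| Months from HCT | All patients | Infused only, day 60 | Infused only, day 30 |
|---|---|---|---|
| 3 | 8.3% | 2.9% | 5.7% |
| 6 | 15.9% | 11.0% | 13.5% |
| 12 | 29.3% | 25.1% | 27.2% |
| 24 | 50.0% | 47.1% | 48.6% |

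A delay of 60 days takes up 1.97 / 3 = 66% of the first reporting window, which is why the distortion is largest at 3 months.

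**Step 3. GVHD before the first CTL.** Let q be the proportion of patients with GVHD from the graft before any CTL. The documents do not give q; it is assumed, and taken as independent of GVHD caused by CTLs. If P1 = 10% refers to GVHD after CTLs and earlier cases are also counted, the rate seen is 1 − 0.9(1 − q). Power is P(X ≤ 2) with 14 patients:

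| q | Rate counted | Power |
|---|---|---|
| 0 | 0.100 | 0.84 |
| 5% | 0.145 | 0.67 |
| 10% | 0.190 | 0.49 |

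If only onset after first infusion is counted, power returns to 0.84 with no change in sample size.

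**The case against.** Much of the opposing case stands.

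- *Allocation is by stored blasts, not by infusion.* Correct. Analysed by that assignment from HCT, with uninfused patients kept in, there is no guaranteed time. But the sentence describing the comparison names treated patients and DLI recipients, so the article supports both readings.
- *The primary objective already restricts GVHD to the period after treatment.* Also correct. A reader might infer that graft GVHD is definitely charged to the product; the documents do not say so. They show two sections that disagree and a count with no stated start.
- *Nothing bars CTLs after relapse.* True. The inclusion criteria admit ALL not in remission at transplant, and the Discussion reports earlier compassionate use in relapsed patients. Only death is certain to keep a patient out of an infused set; the relapse figures above need the extra condition.
- *Culture time does not show a later start for CTLs than for DLI.* The production section says "The time necessary to expand CTL batch 1 is just over a month", which tempts one to infer a longer guaranteed period in the CTL arm. But donor leukapheresis precedes stem-cell mobilisation and blasts are stored at diagnosis or recurrence, so culture need not wait for HCT. DLI timing is not stated. If both arms start together, the between-arm difference in the model above is zero.

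A reader might also infer a spurious benefit of about 6 points. With 50% relapse assumed by 12 months and infusion at month 2, λ = ln 2 / 12 and 1 − exp(−10λ) = 43.9%. The arithmetic is right, but it sets patients all infused at the day-60 maximum against an unselected cohort, over a horizon that the protocol does not state. It is not the bias in the planned comparison.

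**Conclusion.** The concern holds in a conditional form. If infused patients are analysed on a clock from HCT, as the comparison sentence and the reporting times together imply, OS, EFS and NRM are too favourable in absolute terms, and so is relapse if relapsed patients are not infused. In the illustration the relapse estimate is 5.4 points too low at 3 months and about 3 points at 24 months for infusion at day 60, and about half that for day 30. These sizes rest on an assumed constant hazard and horizon. The comparison is biased only if infusion timing, or the share of patients who reach infusion, differs between arms; neither direction nor size can be derived from the documents.

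The conflict over the start of the GVHD risk period does not depend on the analysis set. It bears on the primary decision rule: power would be 0.67 to 0.49 instead of 0.84 if an assumed 5–10% of patients had graft GVHD before the first CTL and it were counted.

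**What to change.** 1. State whether the comparison is by assignment or by treatment received.
2. For the comparison by treatment received, start the clock at first CTL or DLI infusion for relapse, NRM, EFS, OS and GVHD. Alternatively, keep the HCT scale with delayed entry at first infusion. Use the same choice in both groups.
3. Add an analysis from HCT of all patients by blast-availability assignment, infused or not.
4. Reconcile Study objectives with Sample size and data analysis, so that the primary acute GVHD estimate and the rule of two or fewer cases count only onset after first infusion. Report GVHD before infusion separately.

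The cost is analysis wording, plus collection of first-infusion dates for the DLI controls, which the article does not say are recorded. The sample size of 14 + 1 is unchanged.
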